**Methods:**

A multicenter, randomized double-blind, placebo-controlled trial has been designed. Ninety eligible patients will be randomly assigned at a ratio 1:1:1 to one of the following: control group (*n* = 30), low-cell dose treatment group (*n* = 30), and high-cell dose treatment group (*n* = 30). Treatment will be administered in a single-dose way and patients will be followed for 12 months. Primary outcome (safety) will be evaluated by measuring the rate of adverse events within the study period. Secondary outcomes (efficacy) will be measured by assessing clinical, analytical, and imaging-test parameters. Tertiary outcome (quality of life) will be evaluated with SF-12 and VascuQol-6 scales.

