## Background

Critical lower limb ischemia (CLI) is characterized by chronic pain at rest, ulcers or gangrene attributable to a proven occlusive arterial disease [1]. The evolution of CLI, in the context of a generalized atherosclerotic disease, implies high morbidity and mortality. CLI develops earlier and with greater intensity in patients with diabetes mellitus, with complications that may result in the amputation of the limb and even death [2, 3]. A public health goal of the standard of care is to decrease global cardiovascular risk through the control of risk factors by changes on lifestyle habits (quitting smoking, healthy diet, physical exercise) and pharmacological treatment (antiplatelet therapy, statins) [4]. However, there is insufficient evidence to show that this approach improves substantially the course of this disease [5]. Surgical or endovascular revascularization is often the treatment of choice, despite the fact that it is an invasive procedure that carries a high rate of complications. In addition, the health cost of this pathology is quite high. The treatment of the diabetic foot, and specifically critical limb ischemia, is the second most expensive complication in economic terms for the health system, just behind dialysis [6]. Efforts to prevent loss of the affected limb also include soft tissue debridement, minor amputations, and even skin grafts, all of which are costly procedures. In this context, given the high number of amputations that are still practiced annually worldwide, we are still in need of a cost-effective and easy-to-apply treatment [7]. Recently, research has shown that it is possible to improve tissue perfusion through therapeutic angiogenesis, making it one of the most promising strategies used to promote the proliferation of collateral vessels in ischemic tissues. In this sense, there are several methods to improve tissue perfusion, such as the administration of recombinant growth factors [8–11], or the constitutive expression of genes that encode for these factors through gene therapy [12]. Although both therapies have shown to promote angiogenesis in ischemic conditions in preclinical models [13], modest results were obtained when clinically applied [14–17]. In contrast, it has been shown both in animal models and in humans that cell therapy can induce therapeutic angiogenesis [18–20]. Cell-based therapies aiming to promote vascular regeneration gained interest with the discovery of a subpopulation of vasculogenic endothelial progenitor cells as reported by Asahara et al [17]. Human endothelial cell progenitors were isolated from peripheral blood by magnetic bead selection based on cell surface antigen expression. In animal models of ischemia, these cells have the ability to colonize the site of injury of ischemic tissue and secrete a number of vascular growth factors that can lead to clinically effective neovascularization [17]. It seems that these cells contribute to angiogenesis through the secretion of angiogenic cytokines and proteases such as matrix metalloproteases (MMPs), among others, helping the stability and growth of the endothelial and vascular network [21]. In 2002, the pioneering results of the TACT study (Therapeutic Angiogenesis using Cell Transplantation study) were published, consisting of a pilot uncontrolled safety study (*n* = 25) and a randomized controlled clinical trial to evaluate the use of mononuclear cells of bone marrow (BM) by intramuscular injection in 22 patients for treat peripheral arterial disease (PAD). Cell therapy with BM-derived mononuclear cells significantly improved ABI (difference 0.09 [95% CI 0.06–0.11]), transcutaneous oxygen pressure (pTcO2), (13 [9–17]), rest pain (− 0.85 [− 1.6 to − 0.12]) and pain-free walking time (1.2 [0.7–1.7]) in all treated patients [22]. Unfortunately, those with poorly controlled diabetes were excluded from the trial. As the prevalence of PAD increases in patients with type 2 diabetes mellitus (type 2 DM) it is logical to assume that this population group is a potential candidate for cell therapy [22]. Since then, several studies have been carried out in which the transplantation of the mononuclear fraction of BM or peripheral blood has been shown to improve the endothelial function in the territories in which they were administered [23] and to improve ischemic pain and the healing of ulcers [24]. In a phase I/II, open-label, non-comparative clinical trial, safety and feasibility of treatment with autologous mesenchymal stromal cells (MSC) derived from BM and administered intra-arterially in patients with type 2 DM and lower limb ischemia was studied. All of the participants (*n* = 20) showed an increase in leg vascularization demonstrated by angiography and 100% of the ulcers healed. During the first year of follow-up, 7 minor amputations were performed, but no patient suffered a major amputation [25]. Cañizo et al. reported the first case of a patient with CLI treated with peripheral blood CD133+ cells. There were no major amputations and after 17 months of follow-up, patients experienced symptomatic and functional improvement. The group also observed the appearance of blood flow in the posterior tibial artery that was absent before the procedure [26]. The search for the most appropriate cell type for this pathology remains a challenge today [27], but the use of MSC is gaining prominence. The fact that these cells have trophic, immunomodulatory, and anti-inflammatory properties and liposuction is an easy and minimally invasive technique places them as suitable candidates for clinical use. The study that we propose here focuses on the development and optimization of an advanced therapy medicinal product (ATMP) based on adipose tissue-derived MSC (Ad-MSC) to be administered intramuscularly to patients with type 2 DM and CLI within a multicenter randomized phase II clinical trial, favoring the translation of this cellular therapy to clinical practice. If proven safe and effective, an accessible, easy and minimally invasive treatment will be available for patients without any other option or that can even be associated with existing surgical treatments and improve their results.

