### Outcome measures

#### Primary outcome measure

Safety will be assessed comparing the rate of treatment related complications between groups (proportion of treatment related complications among groups) at 24 h and 3, 6, and 12 months from treatment administration, including those related with anesthetic procedure, IMP administration and those occurring after the procedure.

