### Statistical considerations

#### Sample size calculation

A formal size calculation based on the expected differences for the primary outcome has not been performed. This is a phase II, dose-finding study, and no previous data on the preliminary efficacy of Ad-MSC with CLI including type 2 DM patients are available to date. A sample size of 30 patients per group was deemed appropriated based on the possibility to reach normality and the feasibility to recruit 90 eligible patients in 10 university hospitals.

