#### Statistical analysis

Primary, secondary, and tertiary outcomes (safety, efficacy, and quality of life) will be assessed in intention to treat (ITT) and per protocol (PP) populations [39]. ITT population will include all patients who sign the informed consent and receive the investigational product. PP population will include patients who complete the 12-month follow-up period. A descriptive analysis of baseline characteristics of patients included in three groups will be performed. Quantitative variables will be expressed as mean and/or median and standard deviation and/or range. Qualitative variables will be expressed as percentages. When possible, the 95% confidence interval of each of the estimates made will be calculated. To analyze the primary outcomes, 24 h and 3, 6, and 12 months complication rates will be described and compared for the three groups using the Chi-square test or, if necessary, the Fisher exact test. The analyses of the secondary and tertiary outcomes will be performed as follows: qualitative variables will be described in terms of the percentage of improvement of the medical condition in each group and compared using the Chi-square test, or alternatively Fisher’s exact test. VAS scale, SF-12 scale, VascuQuol-6 scale, and the rest of the quantitative variables will be assessed by describing changes in variables at 3, 6, and 12 months from baseline, in an absolute and relative way. Changes at 3, 6, and 12 months in the three groups will be described and compared using the analysis of variance test, or the Kruskal-Wallis test, depending on whether or not the data follow a normal distribution. In all comparisons, a global comparison of the three groups and comparisons between groups by pairing will be carried out (low-dose treatment versus placebo, high-dose treatment versus placebo, high-dose treatment versus low dose, both treatment groups versus placebo). P values will be corrected by Bonferroni test. Regarding handling of missing data, a complete case analysis will be performed if percent of missing data is less than 5%. In another case, a data imputation will be performed for those variables with 25% or less missing values. Variables with more than 25% missing values will be removed from the analysis. The statistical analysis will be carried out by the statistical service of the Jiménez Díaz Foundation University Hospital. Data analyst will be blinded.

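### The primary safety outcome rests on a Bonferroni-corrected test of no difference at 30 per arm, and the planned confidence intervals have no stated role in the safety conclusion

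*Protocol article*

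**What the plan says.** All references are to the protocol article.

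- **Primary outcome measure:** "Safety will be assessed comparing the rate of treatment related complications between groups", at 24 h and 3, 6 and 12 months. Complications of the anaesthetic, of the administration and of the period afterwards all count.
- **Statistical analysis, test:** "complication rates will be described and compared for the three groups using the Chi-square test or, if necessary, the Fisher exact test". A global three-group comparison and four contrasts follow: each dose v placebo, high v low dose, and both doses v placebo. P values are Bonferroni-corrected, and the divisor is not given.
- **Statistical analysis, intervals:** "When possible, the 95% confidence interval of each of the estimates made will be calculated". No sentence links these intervals to the safety conclusion.
- **Sample size calculation:** "A formal size calculation based on the expected differences for the primary outcome has not been performed". The size is justified otherwise: "A sample size of 30 patients per group was deemed appropriated based on the possibility to reach normality", together with feasibility of recruitment.
- **Background:** the hoped-for use is conditional: "If proven safe and effective, an accessible, easy and minimally invasive treatment will be available".

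**The concern.** Chi-square and Fisher tests address the null hypothesis of no difference. They can show harm when harm is large, but failure to reject does not show that harm is absent, and failure becomes more likely as the sample shrinks. The comparison is the stated analysis of the primary outcome, and no other criterion is attached to it. Someone reporting the trial therefore has a p value to cite and no agreed way of using the interval beside it.

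Bonferroni correction adds to the problem. For an efficacy claim it guards against false positives; for a safety comparison it makes a real excess harder to detect.

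At stake is the main message of a dose-finding trial. A clinically important excess at one dose could be reported only as not statistically significant, when the data are in fact compatible with a large excess.

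**Working it through.** **Figure to reproduce.** None. The article states that no size calculation was made for the primary outcome, and gives no rates, power or margin.

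**Inputs from the article.** 30 per arm, 1:1:1; chi-square or, where needed, Fisher; four contrasts, including both doses (60) v placebo (30); Bonferroni correction.

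**Assumptions.** Placebo complication rate 5% or 10%; true excess 15 or 20 points; two-sided alpha 0.05; Bonferroni divisor 4, so 0.05/4 = 0.0125; no dropout; Fisher used when any expected count is below 5, chi-square otherwise.

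**Step 1. Chance of missing the excess.** Miss rate = 1 − Σ Bin(a; n₁, p₁) × Bin(b; 30, p₀), summed over all tables (a, b) in which the test rejects in the harmful direction. Exact enumeration gives:

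| Placebo v active | 30 v 30, 0.05 | 30 v 30, 0.0125 | 60 v 30 pooled, 0.05 | 60 v 30 pooled, 0.0125 |
|---|---|---|---|---|
| 5% v 20% | 72.5% | 85.5% | 59% | 80% |
| 5% v 25% | 51% | 69% | 34% | 57% |
| 10% v 25% | 72% | 86.5% | 63% | 82% |
| 10% v 30% | 53% | 73% | 41% | 65% |

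Outside the assumed band: 20% v 40% is missed 61% of the time at 0.05 (30 v 30), and 10% v 40% is missed 21%. About 80% power for one dose v placebo therefore needs an excess near 30 points (10% v 40%: 79%; 5% v 35%: 84%).

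The choice of test matters. Applied alone at 0.05 to 30 v 30, with a placebo rate of 5–10%, chi-square misses 37–67% and Fisher 56–79%. The table follows the article's switching rule.

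**Step 2. What an interval would show.** Suppose 6/30 on a dose and 1/30 on placebo.
- Fisher: p = 0.103, not significant.
- Risk difference: 0.200 − 0.033 = 0.167.
- Newcombe one-sided 95% upper limit, from the Wilson limits u₁ = 0.3425 and l₂ = 0.0075: 0.167 + √[(0.3425 − 0.200)² + (0.0333 − 0.0075)²] = 0.167 + 0.145 = 0.31.

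The same data give a non-significant test and cannot rule out an excess of 31 points.

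**Step 3. What the planned size can exclude.**
- Zero events, one-sided 95% upper limit 1 − 0.05^(1/n): n = 30, 9.5%; n = 60, 4.9%; n = 90, 3.3%.
- 3/30 in each arm, Newcombe one-sided 95%: 0 + √[(0.2255 − 0.100)² + (0.100 − 0.0407)²] = 0.139, so an excess above about 14 points is excluded. The two-sided 95% limit is 16.9 points.

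**Step 4. The normality rationale.** An arm of 30 expects fewer than 5 events at any rate below 5/30 = 16.7%. Over the assumed placebo rates, a normal approximation is not a basis for sizing a binary outcome.

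**The case against.** The strongest reply is that the article never commits the error. It says that complication rates will be described as well as compared. Its objective is to evaluate safety, not to demonstrate it. The Background sentence is a general hope, and phase III is mentioned only in connection with stratification. It also discloses that the size was not set on the primary outcome. This stands: a reader might infer that p > 0.05 is to be taken as safe, or that a power figure is wrong, and the document supports neither.

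A reader might also infer that no upper bound is planned at all. That is wrong, because 95% intervals are foreseen where possible. What they lack is a role in the conclusion. Detailed interpretation rules may well sit in a full protocol or analysis plan that is not shown. But the article does fix the test, its correction and the sample-size rationale, and those choices can be judged as they stand.

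The normality remark may refer to the quantitative secondary outcomes, where normality decides between analysis of variance and Kruskal-Wallis. That is fair, and the Fisher option covers sparse tables. On that reading, however, the stated rationale tells the reader nothing about the primary outcome.

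Two further claims would go too far. It is not true that any tripling or quadrupling would usually be missed: 10% v 40% is missed only 21% of the time, and pooled 10% v 30% only 41%. Nor is it a serious gap that procedural risks common to all arms cancel in the contrasts, since rates are described for each group anyway.

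Finally, a compulsory pass/fail margin would sit badly with this size. With a true rate of 10% in both arms, one-sided 0.025 and 80% power, 63 per arm are needed for a 15-point margin and 36 for 20 points.

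**Conclusion.** The point holds as a badly chosen basis for inference on the primary outcome. A Bonferroni-corrected difference test at 30 per arm cannot carry a safety conclusion when it is non-significant. With assumed placebo rates of 5–10% and excesses of 15–20 points, one dose v placebo misses the excess in about 51–73% of trials uncorrected, and in about 69–87% with an assumed divisor of four. Pooling the doses helps but does not remove the problem: 59% for 5% v 20% and 41% for 10% v 30%, uncorrected.

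These sizes depend on rates that the article does not give. The logical point does not. Low power is acceptable in a phase II dose-finding study. The change is worth making because it costs only wording and concerns the primary outcome.

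**What to change.** **Statistical analysis.** Make the risk difference in patients with at least one treatment-related complication the basis of the safety conclusion, for each dose v placebo and for both doses v placebo. Give a confidence interval, for example Newcombe, and report its upper limit, without Bonferroni correction. Keep chi-square/Fisher as supplementary. Add one sentence: a non-significant p value will not be taken as evidence of safety. A pre-set acceptable excess is optional and is the sponsor's choice.

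**Sample size calculation.** Do not rely on normality for a binary primary outcome. State instead what the planned numbers can exclude: with zero events, one-sided 95% upper limits of 9.5% (30 patients), 4.9% (60) and 3.3% (90); with 3/30 in each arm, an excess above about 14 points.

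**Cost.** Wording only, with no extra patients or data. The downside is a more modest safety claim, because the trial will have to say openly that it can exclude only fairly large excesses.

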### Blinding, randomization and allocation concealment

Masking of participants will be guaranteed as follows: the solution for intramuscular infusion of Ad-MSC (active treatment) will have the same aspect as HypoThermosolFRS (placebo), and the syringes will be identified by a label that will exclusively contain the information corresponding to the clinical trial and the patient code. However, since the density of each product may be different, it is assumed that there is a risk that the clinical investigator administering the treatment may know which treatment is being applied. For that reason and to ensure double blind, each center will count, as a minimum, with two investigators per enrolled patient: a non-blinded investigator who will administrate cellular therapy and a blinded investigator who will perform the assessment of participants as described in Table 1. Randomization will be performed through the electronic case report form (eCRF). Study subjects will be assigned to group 1, 2, or 3, at a ratio 1:1:1, based in a random block sequence prepared by the sponsor’s statistical service. The assigned group information from each participant will not be visible in the eCRF. Then, an email with the assigned treatment group information of the participant will be sent automatically to non-blinded team. No stratification process has been designed in the randomization scheme. If a phase III clinical trial is subsequently developed, stratification will be defined, according to preidentified factors that could influence efficacy outcomes. During the study, masking can be broken in the event of a serious adverse event (SAE) related to the study medication that requires urgent medical treatment. The researcher will notify the sponsor within a maximum period of 24 h and sign the SAE notification form that will be sent by fax or email to the person in charge of pharmacovigilance of the study. The sponsor will communicate to the investigators any information that may affect the safety of the trial subjects as soon as possible. In the event of unmasking, blinding will be maintained for those responsible for evaluating the primary variable and for those responsible for data analysis and interpretation of the results.

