#### Secondary outcome measures

Efficacy will be assessed through the following variables:

(a) Vascularity in the target limb will be assessed through mean change in percentage of vascular flow measured by MRI in the target limb at 12 months from baseline between groups. MRI will be centrally read by a blinded radiologist. (b) Disease severity will be evaluated through percentage of patients with an improvement in RB category at 3, 6, and 12 months from baseline [33] between groups. This scale is usually used in patients with chronic arterial disease to classify chronic arterial disease into clinical categories (category 0, asymptomatic; category 1, mild claudication; category 2, moderate claudication; category 3, severe claudication; category 4, pain at rest; category 5, minor tissue loss; category 6, ulcer o gangrene). (c) Ulcer healing (if any) will be assessed through the percentage of patients with a decrease in SVS-“WIfI” wound classification [34, 35] at 3, 6, and 12 months from baseline between groups. SVS-WIfI classification aims to be as functional in diagnosing PAD as the tumor-node-metastasis-based diagnosis system (TNM). Three measurable parameters are collected: wound (extension and depth), ischemia (blood flow), and foot infection (presence and extension). (d) PAD evolution will be evaluated by % of patients with an increase in ankle-brachial index at 3, 6, and 12 months from baseline between groups [36]. (e) Pain intensity will be assessed through mean change in visual analogue scale (VAS) from 0 to 10 cm, as described by the patient (0, absence of pain; 1–3, mild; 4–7, moderate; 8–10, severe) and percentage of patients with an improvement in pain intensity at rest at 3, 6, and 12 months from baseline between groups. (f) Percentage of patients with a decrease in temperature (°C), increase in gastrocnemius muscle perimeter (cm) and decrease in neuropathic symptoms of the treated limb compared with contralateral at 3, 6, and 12 months from baseline. (g) Mean change in percentage of amputations in each group at the end of the study will be registered.

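### Quantitative efficacy outcomes are compared as unadjusted changes, with the test picked by a normality check, although baseline values are collected; baseline adjustment would gain precision at almost no cost

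*Protocol article*

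**What the plan says.** All places are in the protocol article.

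- **Statistical analysis.** VAS, SF-12, VascuQoL-6 and the remaining quantitative variables "will be assessed by describing changes in variables at 3, 6, and 12 months from baseline, in an absolute and relative way". The three groups are then "compared using the analysis of variance test, or the Kruskal-Wallis test, depending on whether or not the data follow a normal distribution". No covariate is named. A global test and four contrasts are listed, with Bonferroni correction. The divisor is not stated.
- **Secondary outcome measures, item (d).** "PAD evolution will be evaluated by % of patients with an increase in ankle-brachial index" at 3, 6 and 12 months. No minimum increase is set.
- **Table 1.** VAS, the quality-of-life scales, MRI, ABI and RB category are all recorded at the selection visit (V-1). VAS, quality of life and ABI return at 3, 6 and 12 months; MRI returns only at 12 months.
- **Blinding, randomization and allocation concealment.** "No stratification process has been designed in the randomization scheme". Stratification is put off to a possible phase III trial.
- **Sample size calculation.** "A formal size calculation based on the expected differences for the primary outcome has not been performed". The 30 per group is "based on the possibility to reach normality and the feasibility to recruit 90 eligible patients".

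**The concern.** A change score subtracts the baseline with a fixed coefficient of 1. When baseline and follow-up are imperfectly correlated, that coefficient is too large and baseline noise enters the comparison. ANCOVA estimates the coefficient and removes the excess. The trial enrols RB 4 and RB 5 patients without stratification, so baseline RB category is a natural second covariate, and it is already collected.

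Two related choices add to this. Choosing between ANOVA and Kruskal-Wallis after looking at the distribution means that the effect measure (means or ranks) can differ by variable and by visit. Counting any ABI increase as a response drops the size of the change, so a trivial rise counts the same as a large one.

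With 30 per arm, Bonferroni correction and no power calculation, there is no planned margin to absorb avoidable loss of precision. What is at stake is the trial's ability to see a preliminary efficacy or dose signal.

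**Working it through.** **The plan's own figure.** The only figure to reproduce is 3 × 30 = 90. The article gives no effect size, SD, correlation or power, so those below are assumptions.

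**1. Change score against ANCOVA.** Take equal variance σ² at baseline and follow-up, and correlation r.

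- Variance of change: 2σ²(1 − r)
- ANCOVA residual variance: σ²(1 − r²)
- Ratio: (1 − r²) / [2(1 − r)] = (1 + r)/2
- A difference of d SDs of change becomes d/√[(1 + r)/2] under ANCOVA
- 30 patients under ANCOVA are worth 30 × 2/(1 + r) under change scores

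Power is for one pairwise comparison, 30 per arm, d = 0.6, by noncentral t with 58 degrees of freedom. The change-score noncentrality is 0.6 × √(30/2) = 2.32.

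| r (assumed) | variance ratio | 30 per arm is worth | d under ANCOVA | power, change score | power, ANCOVA |
|---|---|---|---|---|---|
| 0.3 | 0.65 | 46 | 0.744 | 63% | 81% |
| 0.5 | 0.75 | 40 | 0.693 | 63% | 75% |
| 0.7 | 0.85 | 35 | 0.651 | 63% | 70% |
| 0.9 | 0.95 | 32 | 0.616 | 63% | 65% |

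With Bonferroni over the four contrasts (assumed divisor 4, α = 0.0125) and r = 0.5, power goes from about 41% to about 55%. The table covers the baseline value only. Any further gain from RB category is not quantified, because the article gives nothing on how strongly it predicts the outcomes.

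**2. ABI as any increase against mean change.** Assume normally distributed change, no drift on placebo and a 0.7 SD shift on active treatment.

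- Percentage with an increase: Φ(0) = 50% on placebo, Φ(0.7) = 76% on active
- Power, 30 per arm, two-sided 5%: 76% for the mean difference, 54% for the percentages by Pearson chi-square, 44% by Fisher's exact test

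Sensitivity to placebo drift (−0.5, 0 or +0.5 SD) at a 0.75 SD shift, by normal approximation:

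- At 5%: 83% for the mean, against 62%, 60% or 49% for the percentage
- At 0.0125: 66%, against 40%, 38% or 28%
- Patients per arm for 80% power at 5%: 28, against 46, 48 or 62

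**3. Normality-dependent test.** In 4,000 simulated null trials per distribution (3 × 30; Shapiro-Wilk in each arm, then ANOVA or Kruskal-Wallis), the two-stage type I error was 5.0% for normal, 4.3% for lognormal and 5.0% for t with 4 degrees of freedom. With truly normal data the procedure still switched to Kruskal-Wallis in 14% of trials. The switch makes the effect measure inconsistent; it does not inflate error. Power loss from the switch was not examined.

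**4. Relative change.** The VAS runs from 0, meaning no pain, and the eligibility criteria given in the article set no minimum score. Change analysed "in an absolute and relative way" therefore includes a percentage change that is undefined for a baseline of 0.

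**The case against.** **Efficacy is secondary and preliminary, and no power is claimed.** This stands. It limits the weight of the point but does not remove it, since between-group tests with corrected P values are planned.

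**Covariates belong in an analysis plan that is not shown.** This would hold if the article were silent. It names the comparison and the tests, so the point concerns a stated method.

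**The gain depends on an unknown correlation.** This stands. The variance saving is 35% at r = 0.3 and only 5% at r = 0.9.

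**ABI may already be analysed as continuous.** The Statistical analysis section extends the change analysis to all remaining quantitative variables, which could include ABI. The outcome list names only the percentage. It is therefore not established that the size of the ABI change is ignored; the two sections need to be aligned.

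Stronger readings that a reader might draw are not supported:

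- *Baseline data are thrown away.* A change score uses the baseline, only with a less efficient coefficient.
- *All efficacy outcomes are affected.* RB category, WIfI, ABI, temperature, muscle perimeter and neuropathic symptoms are defined as percentages. The change-score point concerns MRI flow, VAS and the two quality-of-life scales.
- *Chance RB imbalance or regression to the mean biases the result.* If half the patients are RB 5, some two arms differ by at least 20 points in RB 5 share with probability 33% (27% if the true share is 30%, 17% if it is 20%). The RB mix is not given. Such imbalance is already allowed for in the type I error of an unadjusted randomised test, and regression to the mean acts equally across arms in expectation.
- *The normality check inflates false positives.* The simulation does not show this.

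**Conclusion.** The planned comparison of quantitative outcomes is valid but less precise than the collected data allow. For a 0.6 SD difference at 30 per arm and two-sided 5%, baseline adjustment lifts power from 63% to between 65% and 81%, for r from 0.9 down to 0.3. The correlation, effect size, equal variances and Bonferroni divisor are assumptions.

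For ABI the loss is larger (about 54% against 76%), but only if the percentage with any increase is the sole test, and given an assumed 0.7 SD shift with no placebo drift. The article leaves open whether that is so.

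The normality-dependent choice is a weakness of pre-specification, and relative change is a minor definitional fault because absolute change is also reported. The point is a worthwhile efficiency improvement for secondary outcomes.

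**What to change.** 1. Replace the choice between ANOVA and Kruskal-Wallis with a pre-specified ANCOVA for each quantitative outcome, adjusting for its baseline value and baseline RB category. Keep a rank-based analysis as sensitivity.
2. For outcomes measured at 3, 6 and 12 months, a repeated-measures model with the same covariates is an alternative. It cannot be used for MRI, which has a single follow-up; use ANCOVA at 12 months there.
3. State in both the outcome list and the Statistical analysis section that ABI is compared as a continuous, baseline-adjusted outcome, with the percentage showing an increase as supportive.
4. Base inference on absolute change. If relative change is kept, make it descriptive and say how a baseline of 0 is handled.

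Cost: analysis wording, slightly more modelling and a few degrees of freedom. No new data, visits or patients are needed, since every covariate is already recorded at V-1.
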